##### Secondary endpoint analyses

Linear regression analysis (ANCOVA) will be used to examine the effect of the randomised intervention on the OSS at 12 months postrandomisation, using three two-way comparisons. The model will be adjusted for appropriate baseline measurements. In addition, a repeated-measures multilevel model will be used, including repeated measures of the OSS at 6 and 12 months (level 1) nested within participants (level 2). Adjustments will be made for the continuous baseline OSS, other relevant minimisation factors and baseline measures as appropriate. Additional supplementary analyses will take into account long waiting times before surgery. As described for the primary analysis, analyses will include substituting the baseline and 12 months postrandomisation data for data collected presurgery and at approximately 12 months postsurgery, respectively, for participants with a delay longer than 16 weeks before surgery. In sensitivity analyses, we will look at the impact of a patient response shift on perceived disability by comparing each patient’s preoperative self-evaluation of his or her own disability (baseline OSS) with a 12-month evaluation of perceived preintervention state (the ‘thentest’) according to the method of Razmjou *et al*. [46]. This analysis will give an indication of whether patients with subacromial pain underrate or overrate their preintervention disability according to their outcome. The response shift will be presented descriptively using medians, interquartile ranges and ranges overall, as well as by treatment arm. The effect of the response shift and perceived disability will be investigated by refitting the above-described linear regression model for the OSS at 12 months postrandomisation, adjusting for continuous retrospective baseline OSS (thentest), as well as other relevant minimisation factors and baseline measures. Differences in the treatment effects using this approach and the previously described model for the analysis of the 12 months postrandomisation OSS will be highlighted.

The Constant-Murley shoulder score, PainDETECT, quantitative sensory test, Hospital Anxiety and Depression Scale and EQ-5D (index score and Visual Analogue Scale) measures will be scored according to their respective scoring manuals. Linear regression analysis (ANCOVA) will be used to analyse the 6- and 12-month outcomes, respectively, and a repeated-measures multilevel model will be fit (see above). The analysis will be adjusted for the relevant minimisation factors and baseline measures as appropriate.

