**Table 1 Tab1:** **Timetable of assessment**
^**a**^

**Assessment**	**Baseline**	**6 mo**	**1 yr**	**1 yr posttreatment (for waiting list breachers only)**
OSS (self-reported pain and function)	▲	▲	▲	▲
Constant-Murley shoulder score	▲	▲	▲	▲
QST and PainDETECT	▲	▲	▲	▲
EQ-5D (health economics)	▲	▲	▲	▲
Health service use		▲	▲	
Treatment expectations and patient satisfaction	▲	▲	▲	▲
Complications	N/A	▲	▲	▲
Patient response shift	N/A	N/A	▲	▲
Hospital Anxiety and Depression Scale	▲	▲	▲	▲

^a^N/A, Not applicable; OSS, Oxford Shoulder Score; Quantitative sensory testing. All information is postrandomisation, unless stated otherwise.

▲Outcome measure to be collected at this assessment.

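### The 12-month response-shift refit adjusts for a recall score taken at 12 months, so its arm coefficient can be biased as a treatment effect

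*Protocol article*

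**What the plan says.** All of this is in the protocol article, mostly under Secondary endpoint analyses.

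- The main 12-month OSS analysis is an ANCOVA: "The model will be adjusted for appropriate baseline measurements".
- Response shift is introduced as a side question: "In sensitivity analyses, we will look at the impact of a patient response shift on perceived disability". The method compares baseline OSS with a "12-month evaluation of perceived preintervention state", the thentest.
- The aim is to learn "whether patients with subacromial pain underrate or overrate their preintervention disability according to their outcome".
- Response shift is first summarised descriptively, overall and by arm. The 12-month regression is then refitted, "adjusting for continuous retrospective baseline OSS (thentest), as well as other relevant minimisation factors and baseline measures".
- The result is reported as follows: "Differences in the treatment effects using this approach and the previously described model for the analysis of the 12 months postrandomisation OSS will be highlighted".
- In Table 1 the row "Patient response shift" is not applicable at baseline and 6 months. It is collected at 1 year and, for patients who waited too long for surgery, at 1 year after treatment.
- Under Blinding, patients are blinded in the two surgical groups only. In the AMSR group only the assessors are blinded.

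**The concern.** A randomised comparison adjusted for a variable measured before randomisation keeps its meaning as a treatment effect. The thentest only looks like such a variable. It refers to the past but is recorded at the 12-month assessment, like the outcome. Two routes can make it differ between arms:

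- **Through the outcome.** The protocol itself expects recall to vary with outcome. If treatment changes the outcome, mean thentest then differs by arm. This applies to the blinded ASAD versus AO contrast too.
- **Through knowledge of allocation.** AMSR patients know that they had no operation, which may colour how they remember their earlier state.

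The refit is a stated choice, and nothing in the section cautions about the timing of the covariate. At stake is how a highlighted gap between the two models would be read. A reader could take it as doubt about, or support for, the 12-month result, or as the size of the effect of response shift. It is a sound measure of neither.

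**Working it through.** **The plan's own figure.** The only design calculation is the sample size (Sample size calculation): difference 4.5, SD 9.0, two-sided 5%, 90% power. The normal approximation gives 2 × (1.960 + 1.282)² × (9/4.5)² = 84.1, so 85 per group; the t-test version gives 85.03. Then 85/0.85 = 100. The plan's figures reproduce and are not in dispute. They supply the scale: 4.5 points is the target difference, and 9.0 is the SD of change in OSS.

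**General result.** Let Y be 12-month OSS, B measured baseline OSS, T the thentest, δ the true effect and b the within-arm slope of Y on T. With T as covariate in place of B,

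arm coefficient = δ − b × (arm difference in mean T).

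The bias is zero if the arms do not differ in mean T, or if T does not predict Y.

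**Inputs.** The documents give no correlation, recall dependence or arm shift, so these are assumptions. B and Y each have SD 9 with correlation 0.5. This gives SD of change √(81 + 81 − 2 × 40.5) = 9, which matches the protocol. Recall is T = B + k(Y − B) + s × arm + noise, with noise SD 4. Here k is the share by which recall moves toward (positive) or away from (negative) the current state, and s is a direct shift by arm.

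- Cov(Y,T) = (1 − k) × 40.5 + k × 81
- Var(T) = (1 − k)² × 81 + k² × 81 + 2k(1 − k) × 40.5 + 16
- Arm difference in T = kδ + s

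| δ | k | s | Cov | Var | b | Arm difference in T | Estimate |
|---|---|---|---|---|---|---|---|
| 4.5 | 0.2 | 0 | 48.60 | 84.04 | 0.578 | 0.9 | 3.98 |
| 4.5 | 0.4 | 0 | 56.70 | 77.56 | 0.731 | 1.8 | 3.18 |
| 4.5 | −0.2 | 0 | 32.40 | 116.44 | 0.278 | −0.9 | 4.75 |
| 0 | 0 | −2 | 40.50 | 97.00 | 0.418 | −2 | 0.84 |
| 0 | 0 | −4 | 40.50 | 97.00 | 0.418 | −4 | 1.67 |

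Reversing the sign of s reverses the sign of the last two estimates.

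**Second recall model, by simulation.** Here T = B + s × arm + k(Y − 0.5B) + noise with SD 5, k runs from −0.4 to 0.4, s is 0, −2 or −4, and each setting has 400,000 patients.

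- Thentest replaces B: a true 0 is estimated at 0.0 to 2.2, and a true 4.5 at 3.48 to 6.05.
- Measured B as covariate: the estimate is within 0.1 of the truth in every setting.

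**If the thentest is added to B instead of replacing it.** The variance of Y given B is 81 × 0.75 = 60.75. The slope on T given B is c = 60.75k/(60.75k² + 25), and the arm coefficient is δ − c(s + kδ). With k = ±0.4, c = ±24.3/34.72 = ±0.700.

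- δ = 0, s = −4: ±0.700 × 4 = ±2.80.
- δ = 4.5, s = −4, k = −0.4: 4.5 − 0.700 × 5.8 = 0.44 (simulated 0.45).
- δ = 4.5, s = −4, k = 0.4: 4.5 + 0.700 × 2.2 = 6.04 (simulated 6.08).

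Keeping B in the model does not remove the problem.

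**Does the gap between models measure response shift?** Two settings of the second recall model, with the thentest replacing B, show that it does not. With δ = 0, s = 0 and k = 0.4, recall depends on outcome, yet both models estimate 0. With δ = 4.5, s = −2 and k = 0.4, both recall mechanisms act but nearly cancel: the arm difference in T is −2 + 1.8 = −0.2, and the simulated estimates are 4.62 and 4.52.

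**The case against.** The strongest reply is about reach. The refit is labelled a sensitivity analysis of a secondary outcome, and the baseline-adjusted model stays as the reference. Nothing says that the thentest-adjusted coefficient replaces the main estimate or supports a conclusion. That stands, and it limits the weight of the point.

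Four stronger readings are tempting, and the protocol does not support them.

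- **That the primary objective is at risk.** The primary outcome is OSS at 6 months, and Table 1 does not collect response shift then. The ASAD versus AMSR contrast recurs at 12 months, but the primary estimate cannot be touched.
- **That the refitted effect must be biased.** Bias needs both an arm difference in mean thentest and a thentest that predicts OSS. With pure recall noise there is none.
- **That a gap between the models means nothing.** In the recall models above, a gap in expectation arises only when recall depends on outcome or arm, so it may signal differential recall. It does not measure the effect of response shift, and in a finite sample the two fits also differ by chance.
- **That measured baseline OSS is certainly discarded.** The word other in "adjusting for continuous retrospective baseline OSS (thentest), as well as other relevant minimisation factors and baseline measures" makes replacement the likelier reading. But the sentence also admits further baseline measures, and baseline OSS is a minimisation factor. The text does not settle it, and the problem remains either way.

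It is also fair to say that the magnitudes are illustrative, since no recall parameter comes from the documents.

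**Conclusion.** The point holds as a limited one that should be corrected. The refit conditions on a post-randomisation covariate that the protocol itself expects to vary with outcome, and it presents the resulting coefficient as a treatment effect. That coefficient can be biased in either direction.

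Under the first set of assumptions, a true 4.5 becomes about 3.2 to 4.75, and a true 0 moves by up to about 1.7 points. Other plausible recall assumptions give wider ranges. Against a target difference of 4.5 points the distortion can be material. Of the inputs, only the SD of change of 9.0 and the 4.5-point difference come from the protocol.

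The 6-month primary analysis, the main 12-month ANCOVA, the sample size and the error rates are not affected.

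**What to change.** - Keep prerandomisation OSS as the covariate in every model that estimates a treatment effect.
- Analyse response shift, defined as thentest minus baseline OSS, as an outcome compared between arms and adjusted for baseline OSS and the minimisation factors. Report it beside the descriptive summaries already planned.
- Either drop the thentest-adjusted refit, or keep it as exploratory with a statement that its arm coefficient is not an estimate of the treatment effect.

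This takes a sentence or so of text and a little more analysis, with the same data and software. The price is the loss or demotion of one prespecified sensitivity analysis.

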### Complications

Complications between the trial arms will be compared in terms of frequency, seriousness and timing. To coincide with the primary endpoint, complications occurring within the initial 6 months from randomisation will be summarised first; complications reported over the entire duration of the trial will be reported separately. Logistic regression analysis with covariate adjustment will be carried out to test the difference in the proportion of participants with at least one complication, given sufficient events.

### Treatment expectations and patient satisfaction

Treatment expectations will be summarised descriptively using medians, interquartile ranges and ranges overall, as well as by treatment arm. Patient satisfaction with treatment will be summarised descriptively by treatment arm for the 12-month time point. Cross-tabulations will be generated to relate treatment expectations to treatment satisfaction, and χ^2^ tests will be used to assess the significance of the association.

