### Objectives

The primary objective is to compare ASAD against a nonsurgery arm (the AMSR group) to assess efficacy. In addition, both ASAD surgery and AMSR will be separately compared with investigational shoulder arthroscopy (the AO group) to delineate the mechanism of any benefit. The primary outcome measure is the Oxford Shoulder Score (OSS) at 6 months.

Secondary objectives include the comparison of the three treatment arms in the CSAW Study with regards to other variables—namely, cost-effectiveness, self-reported outcomes (OSS) at 12 months, shoulder function, range of motion, pain, complications, treatment expectations and patient satisfaction, anxiety and depression.

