#### Secondary outcome measures

The following are the secondary outcome measures:OSS at 12 months postrandomisationConstant-Murley shoulder score: assesses shoulder function and range of motion and is commonly used by health care practitioners [40]PainDETECT: a patient-based screening questionnaire used to predict the prevalence of neuropathic pain components that has been widely used in many areas of musculoskeletal care [41]Quantitative sensory testing: measures pain and pain thresholds (This is a modified form of the full quantitative testing and was validated by Gwilym *et al*. in 2009 [42].)Complications during and after the treatment.EQ-5D: a measure of general quality of lifeHealth service use: measures the cost utilisation associated with the treatmentsTreatment expectations: Expectations will be assessed using two different scores. The first score was developed by Henn *et al*. [43] and is calculated using the Treatment Expectations Questionnaire. This questionnaire asks six general questions about pain and function. More shoulder-specific expectations will be predicted by asking patients to state how they expect to feel and function in 12 months’ time using the OSS.Patient satisfaction: Patient satisfaction will be assessed using the Oxford Satisfaction Index. This index includes transition questions developed and used recently by members of the study team to measure patients’ satisfaction after shoulder surgery [44].Anxiety and depression: The Hospital Anxiety and Depression Scale will be used to detect states of depression and anxiety in the setting of a hospital medical outpatient clinic [45].

The timing of all assessments is shown in Table 1 as a schedule of events. It is acknowledged that there are many outcome assessments, and questionnaire fatigue may be an issue. This will be closely monitored. Poor response rate to follow-up will be used as a marker of questionnaire fatigue.

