#### Active monitoring with specialist reassessment

Patients will be advised that they will undergo active monitoring. They will attend a reassessment appointment 3 months after entering the study. At that appointment, they will be asked to complete questionnaires related to their shoulder pain and undergo a clinical assessment of the shoulder, including a record of any further conservative treatment. If, at the end of the 6-month assessment period, patients remain sufficiently symptomatic to require further intervention (based on clinical judgement), then additional treatment options will be discussed. It should be noted that the inclusion criteria state that all patients will have undergone conservative treatment (including physiotherapy and injection) before entering the trial. From an ethical standpoint, it is emphasised that it is quite within normal practice to have a period of active monitoring.

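### Comparing the arms on patient satisfaction is a secondary objective, but the stated analysis is a descriptive 12-month summary with no between-arm estimate or interval

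*Protocol article*

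**What the plan says.** In the protocol article:

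- **Objectives.** "Secondary objectives include the comparison of the three treatment arms in the CSAW Study with regards to other variables". The list that follows includes "treatment expectations and patient satisfaction, anxiety and depression".
- **Secondary outcome measures.** "Patient satisfaction will be assessed using the Oxford Satisfaction Index". On its format the article says only "This index includes transition questions developed and used recently by members of the study team". The number of categories, their order and any scoring rule are not given. Expectations are measured by a six-question score and by an OSS completed for how the patient expects to be in 12 months.
- **Table 1.** One joint row, "Treatment expectations and patient satisfaction", is marked at baseline, 6 months, 1 year and, for waiting-list breachers, 1 year after treatment.
- **Treatment expectations and patient satisfaction.** Expectations are summarised by medians, interquartile ranges and ranges. For satisfaction, "Patient satisfaction with treatment will be summarised descriptively by treatment arm for the 12-month time point". Expectations and satisfaction are then cross-tabulated, and chi-square "tests will be used to assess the significance of the association".
- **Secondary endpoint analyses and Complications, for contrast.** Constant-Murley, PainDETECT, quantitative sensory testing, the Hospital Anxiety and Depression Scale and EQ-5D get ANCOVA at 6 and 12 months plus a repeated-measures model. Complications get a covariate-adjusted logistic regression if events suffice.

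**The concern.** The objective promises a comparison of arms, and the analysis section chooses something weaker. It does not leave the method open for the statistical analysis plan: it names a descriptive summary and one time point. Followed as written, the report would show satisfaction by arm with no statement of how large a difference the data support or exclude, although neighbouring secondary outcomes have one. A 6-month reading, if taken, would have no stated use.

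A second, separate point concerns the only test that involves satisfaction. It relates expectations to satisfaction, not arm to satisfaction. Expectations are treated as ordered when summarised by medians and quartiles, and then as unordered when tested by chi-square.

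**Working it through.** **1. Objective against analysis.** Taking the listed variables in turn, OSS at 12 months, shoulder function and range of motion, pain, anxiety and depression, and complications each have a stated between-arm model. Cost-effectiveness is referred to its own plan. Satisfaction has a by-arm description. Expectations are also only described, but they are measured at baseline, before treatment, where description is natural. Satisfaction with treatment is an outcome, and no reason is given for handling it differently from the others.

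**2. Time points.** The Table 1 row is marked at 6 months, but it is shared by two items and is also marked at baseline, when satisfaction with trial treatment cannot yet exist. The marks therefore need not apply to both items at every visit. Collection of satisfaction at 6 months is likely but not certain.

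**3. Precision available.** The plan's own figure comes first. With difference 4.5, SD 9.0, two-sided 5% and 90% power, n = 2 × (1.960 + 1.282)² × (9.0/4.5)² = 84.1, rounded up to 85 per group. The t-test solution is 85.03. Allowing 15% loss, 85/0.85 = 100 per group, or 300 in all. The stated figures are reproduced.

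With 85 evaluable per arm, a 95% interval for a difference in proportion satisfied has half-width 1.96 × √(2p(1 − p)/85). The proportion p is an assumption, since the article gives none:

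| Assumed p | Half-width |
|---|---|
| 0.5 | 15.0 points |
| 0.7 | 13.8 points |
| 0.8 | 12.0 points |

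This is the uncertainty that a bare by-arm table leaves unstated.

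**4. Chi-square against an order-respecting test.** Assumptions: expectations and satisfaction each fall into four equally frequent ordered categories, N = 3 × 85 = 255, with an underlying bivariate normal association. Pearson chi-square (9 df) was compared with the linear-by-linear test, (N − 1)r² on 1 df, in 3,000 simulations per row:

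| Latent correlation | Chi-square | Linear-by-linear |
|---|---|---|
| 0 (type I error) | 4.1% | 4.3% |
| 0.10 | 12% | 28% |
| 0.15 | 23% | 52% |
| 0.20 | 42% | 79% |
| 0.25 | 66% | 93% |
| 0.30 | 85% | 99% |

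Both tests hold their level. The loss is power, and it is largest for modest associations.

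**The case against.** Much of the case for the plan stands.

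- **A description by arm is a comparison of a kind.** The objective says comparison, not hypothesis test. A reader might infer that the trial cannot address satisfaction at all. The documents do not support that: a by-arm summary is planned, and what is missing is an estimate with an interval or a test.
- **The two points are not linked.** A reader might take the chi-square as the reason the between-arm objective goes unmet. It is not, because that test does not involve arm. For the same reason, power figures for a chi-square of arm by satisfaction would be beside the point: no such test is planned.
- **Six months is not the better time point.** One might argue that 6 months should lead because it matches the primary endpoint, and because symptomatic AMSR patients have a discussion after it ("then additional treatment options will be discussed"), which blurs 12 months. But surgery is expected within 4 months and may come later, and the Primary endpoint analysis section accepts that long-wait patients may not have recovered fully by 6 months. The shoulder-specific expectation question also looks 12 months ahead. Each time point has its own difficulty.
- **The ordering of the satisfaction items is assumed.** Chi-square is valid either way and can detect non-monotone patterns that a trend test may miss.
- **Detail may sit in the analysis plan.** The article announces one and allows alternative methods. That covers the choice of model. It does not remove the mismatch between an objective and an analysis that are both stated here.
- **Multiplicity.** Three contrasts at two times add six estimates, and the sample size section makes no adjustment for multiple comparisons. If each were tested at 5% with no true differences, 6 × 0.05 = 0.3 false positives would be expected. Estimates with intervals, labelled secondary, are a proportionate answer.

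**Conclusion.** The mismatch holds as a minor point. Between-arm comparison of satisfaction is a stated secondary objective, and the stated analysis stops at description at 12 months. No between-arm estimate, interval or test is given, and no use is stated for a 6-month reading. This rests on the article's wording alone; the 6-month part also depends on the shared Table 1 row applying to satisfaction.

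The chi-square point holds conditionally. Expectations are handled as ordered in the same section. If satisfaction is ordered too, the chi-square gives up power against a monotone association, about 42% against 79% in the illustration at correlation 0.20. That figure depends on the assumed 4x4 layout and N of 255. Type I error is not at risk.

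Nothing here touches the primary OSS analysis, the other modelled secondary outcomes or the sample size.

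**What to change.** Choose one of two routes for the objective:

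1. Analyse satisfaction at 12 months, and at 6 months where it was collected, by ordinal regression (or another model suited to the scoring of the index). Report the three pairwise contrasts with 95% confidence intervals, adjusted for the minimisation factors as for the other secondary outcomes. Report both times without ranking one above the other, and state in Table 1 which item of the joint row is taken at which visit.
2. Or reword the Objectives section so that satisfaction is a descriptive objective.

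Separately, replace the chi-square with a linear-by-linear trend test, or with ordinal regression of satisfaction on expectation, provided the satisfaction items are ordered. Keep the cross-tabulations so that non-monotone patterns remain visible.

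The cost is a few lines of analysis on data already scheduled, with no extra patients or visits. The downsides are up to six more secondary contrasts without multiplicity adjustment and less sensitivity to non-monotone association.
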